## Abstract

**Background:**

Irreversible electroporation (IRE) is an emerging technique delivering electrical pulses to ablate tissue, with the theoretical advantage to overcome the main shortcomings of conventional thermal ablation. Recent short-term research showed that IRE for the ablation of renal masses is a safe and feasible treatment option. In an ablate and resect design, histopathological analysis 4 weeks after radical nephrectomy demonstrated that IRE-targeted renal tumors were completely covered by ablation zone. In order to develop a validated long-term IRE follow-up study, it is essential to obtain clinical confirmation of the efficacy of this novel technology. Additionally, follow-up after IRE ablation obliges verification of a suitable imaging modality.

**Objective:**

The objectives of this study are the clinical efficacy and safety of IRE ablation of renal masses and to evaluate the use of cross-sectional imaging modalities in the follow-up after IRE in renal tumors. This study conforms to the recommendations of the IDEAL Collaboration and can be categorized as a phase 2B exploration trial.

**Methods:**

In this prospective clinical trial, IRE will be performed in 20 patients aged 18 years and older presenting with a solid enhancing small renal mass (SRM) (≤4 cm) who are candidates for ablation. Magnetic resonance imaging (MRI) and contrast-enhanced ultrasound (CEUS) will be performed at 1 day pre-IRE, and 1 week post-IRE. Computed tomography (CT), CEUS, and MRI will be performed at 3 months, 6 months, and 12 months post-IRE.

**Results:**

Presently, recruitment of patients has started and the first inclusions are completed. Preliminary results and outcomes are expected in 2018.

**Conclusions:**

To establish the position of IRE ablation for treating renal tumors, a structured stepwise assessment in clinical practice is required. This study will offer fundamental knowledge on the clinical efficacy of IRE ablation for SRMs, potentially positioning IRE as ablative modality for renal tumors and accrediting future research with long-term follow-up.

**Trial Registration:**

Clinicaltrials.gov registration number NCT02828709; https://clinicaltrials.gov/ct2/show/NCT02828709 (archived by WebCite at http://www.webcitation.org/6nmWK7Uu9). Dutch Central Committee on Research Involving Human Subjects NL56935.018.16

## Introduction

### Ablative Therapy in Renal Cell Carcinoma

Due to widespread detection of small renal masses (SRMs), a gradual but sustained rise in incidence of renal tumors 4 cm or less (cT1a, according to the TNM [tumor/node/metastasis] staging system) has been observed [1-4]. At present, the reference standard therapy in the management of SRMs is nephron sparing surgery like partial nephrectomy [5]. However, a significant interest is sparked in minimally invasive therapies, including cryoablation and radiofrequency ablation (RFA). Literature shows that thermal ablation compared to partial nephrectomy is characterized by a slightly higher recurrence rate but also accompanied by a lower complication rate [6,7]. Nevertheless, a growing body of research advocates that in selected patients similar oncological results can be obtained compared to those accomplished in surgical resection [8]. Current guidelines recommend primary ablative therapy in patients who are (1) not suitable for surgery, (2) have a genetic predisposition for developing multiple tumors, and (3) are diagnosed with bilateral tumors or have a solitary kidney and are at risk of complete loss of renal function after surgery [9-11].

Ablation of undesirable tissue depends on accurate dosing and adequate targeting of tumor destruction while sparing vital structures such as adjacent organs, collecting system, or major vessels [12,13]. Due to temperature fluctuations that are accompanied with the thermal character of cryoablation and RFA, it is thought that the destruction process of the tumor is unselective [14,15]. Ablation effects and tissue heating may be less effective in proximity to blood vessels as a result of thermal drainage by regional vascular flow impairing the extent of coagulation, in the literature termed as a “heat sink” effect [9,16]. Additionally, collateral damage to underlying vital structures can occur, as the natures of these structures are susceptible to extreme temperatures. Therefore according to guidelines, renal tumors located near the hilum or near the proximal ureter are not suitable for thermal ablation, forming a niche in ablative treatment of renal tumors [10].

### Irreversible Electroporation in Renal Cell Carcinoma

An emerging technique among the assortment of ablative modalities is called irreversible electroporation (IRE). It is based on high-voltage electrical pulses transferred between 2 or more needle electrodes. Charging the cell membrane causes holes in the membrane called nanopores, resulting in increased permeability of the cell and subsequent cell death [13,17-20].

Theoretically, the mechanism of action of IRE does not rely on temperature changes. Therefore it has been postulated that it has the potential to overcome the current limitations of thermal ablative modalities like cryoablation and RFA [12]. However, using the current clinical device settings, a rise in temperature is to be expected as shown by Wagstaff et al in an animal model [21].

With regard to IRE ablation in renal tumors, 4 studies have been performed in humans [20,22-24]. All studies concluded that safety of IRE in humans is warranted as long as electrocardiogram (ECG) synchronization is used.

Trimmer et al made a start in clinical efficacy, describing postablation features on cross-sectional imaging. Although these initial results seem promising and appear similar to conventional ablative techniques, a few limitations deserve consideration. The study design is retrospective, and the follow‐up was limited. Imaging was available in 15 out of 20 patients (75%) at 6-month follow-up and only in 6 out of 20 patients (30%) at 1-year follow-up [23].

Thomson et al performed IRE in various organs, including 10 renal tumors in 7 patients. One patient (14%) developed an ureteral stricture after IRE ablation in an area of the ureter that previously had been obstructed by RFA. Other centrally located tumors did not show any major complications. A total of 2 patients (29%) experienced minor complications consisting of transient hematuria [24]. Wendler et al were the first to provide histopathological data of IRE in renal tumors of 3 patients, showing complete coverage of the tumor within the ablation zone with preservation of the renal parenchyma [25]. Very small tumor residues of unclear malignant potential were found within the ablation zone. Unfortunately, clinical significance of these residues remained unclear and impossible to follow up since the tumors had been resected.

### Rationale

The first human studies have proven the safety of IRE for the ablation of SRMs. Initial results on clinical efficacy of IRE are promising and imply that effective oncological management is achievable. Clinical outcomes should be investigated in a small patient population to provide essential data before embarking on a randomized trial. We therefore plan to perform a study aiming at the clinical efficacy and safety of IRE in SRMs, with a specific focus on postablation follow-up with cross-sectional imaging. Research on IRE in liver tumors has demonstrated that ablation success of IRE decreases with tumor size above 4 cm [24]. According to current guidelines, ablative treatment is only offered to patients with SRMs (≤4 cm) [10]. Therefore, we aim to investigate IRE ablation in renal masses up to 4 cm. This prospective, human, in vivo trial is an essential step in order to safely progress to larger randomized trials on IRE of SRMs. This study conforms to the recommendations of the IDEAL (idea, development, exploration, assessment, long-term study) Collaboration and can be categorized as a phase 2B exploration trial [26] *.*

## Methods

### Study Objectives

To determine the clinical efficacy of IRE ablation for SRMs (≤4 cm) assessed by the recurrence and residual disease rate at follow‐up using cross‐sectional imagingTo evaluate the use of computed tomography (CT), magnetic resonance imaging (MRI), and contrast-enhanced ultrasound (CEUS) in the visualization of (non)complete ablation to assess the radiological extent of the ablation zone at 1 week, 3 months, 6 months, 9 months and 1 year after IRETo evaluate perioperative outcomes after IRE ablation of SRMs (≤4 cm) such as (1) renal function, measured by creatinine levels and estimated glomerular filtration rate (eGFR), (2) average length of hospital stay, (3) quality of life, and (4) postoperative pain score after IRE, measured by a visual analog scale (VAS) and analgesics useTo determine the safety and feasibility of IRE ablation of SRMs (≤4 cm) by evaluating device and procedural adverse events using Common Terminology Criteria for Adverse Events (CTCAE) version 4.0

### Population

A total of 20 patients with solid enhancing SRMs on cross-sectional imaging qualifying for ablative therapy will be enrolled in this study. Eligible patients are 18 years of age and older and will receive a biopsy of the SRM before procedure. All inclusions are reviewed for safety and eligibility by a nephrologist participating in the research project. The inclusion and exclusion criteria for this study are listed in Textbox 1.

Selection criteria. Severe cardiovascular disease is defined as the diagnosis of myocardial infarction, uncontrolled angina, significant ventricular arrhythmias, stroke or severe cardiac failure (New York Heart Association class III and IV) within 6 months prior to inclusion.Inclusion criteria:Age 18 years and olderSolid enhancing SRM on cross-sectional imagingCandidate for ablationSigned informed consentExclusion criteria:Irreversible bleeding disordersInability to stop anticoagulation therapyImplantable cardioverter-defibrillator or pacemakerSevere cardiovascular disease

### Study Design

This is a prospective, human, in vivo study among 20 patients presenting with solid enhancing SRM on cross-sectional imaging suspect for RCC. Preoperatively, imaging is required through CT, MRI, and CEUS. Furthermore, serum creatinine levels and VAS scores are obtained. A biopsy of the SRM will be performed prior to the ablation. IRE ablation will be performed using CT guidance, and ablation success will be measured directly after the ablation through contrast-enhanced CT. Device-related adverse events will be registered using the CTCAE version 4.0 guideline. At 1 week postablation, only CEUS and MRI will be performed to limit exposure to ionizing radiation. At 3 months, 6 months, and 12 months postablation, CEUS, MRI, and CT will be performed. Additionally at these time points, serum creatinine levels and VAS scores will be obtained, and quality of life will be assessed through Short Form 36 (SF-36) questionnaires. Residual and recurrent disease will be assessed through tissue enhancement on cross-sectional imaging. When imaging appears suspicious for recurrence or residual disease, a percutaneous renal core biopsy will be performed. A study flowchart demonstrating the investigations is outlined in Figure 1.

**Figure 1 figure1:**
[figure not shown]
Study design flowchart.

### Study Procedures

#### Renal Core Biopsy (Standard)

According to the ablation protocol of the Academic Medical Center University Hospital, percutaneous renal core biopsies will be obtained prior to the IRE procedure if patient desires. At least 2 core biopsies will be acquired for pathological examination.

#### Irreversible Electroporation Ablation (Study Intervention)

In this study, IRE ablation is performed using the NanoKnife IRE device (AngioDynamics Inc) (Figure 2, A), also registered as the HVP-01 electroporation system. The IRE system contains a low energy direct current generator, a foot switch, and 19G monopolar needle electrodes (15 or 25 cm length). Regulatory authorities have approved both the device and the electrodes through a Conformité Européenne certificate for the use of cell membrane electroporation. Additionally, the US Food and Drug Administration has granted 510(k) clearance with premarket notifications (K060054, K080202, K080376, K080287). Granted 510(k) components are all approved for surgical ablation of soft tissue.

The IRE procedure will be performed at the radiology department CT room with the patient under general anesthesia including deep muscle relaxation to prevent severe muscle contraction [27]. CT imaging will be performed with the patient in the prone or lateral position, dependent on tumor location and position of adjacent organs such as intestines. An interventional radiologist cooperating with a urological surgeon, both experts on percutaneous ablative procedures, will perform the IRE procedure. IRE pulses will be synchronized with ECG under supervision of an anesthesiologist. Prior to ablation, a (second) set of biopsies will be obtained to confirm histopathology. Guided by CT and accompanied by an external spacer for fixation, needle electrodes will be placed (Figure 2, B). The amount of probes and probe placement will be attuned for specific tumor size and location, granting 15 mm between the electrodes with an active tip length of 15 mm. IRE pulses with pulse intensity of 1500 V/cm will be delivered in 90 consecutive pulses of 90 µs *.* Settings are used to disrupt the cell membrane potential in order to achieve irreversible permeability of the cell and subsequent apoptosis. Van den Bos et al demonstrated that with current settings the ablation zone is completely ablated without leaving any skip lesions within the electrode configuration [28].

The primary cycle of IRE will take 5 to 10 minutes with a total operating time (including anesthesia) of approximately 90 minutes. Immediately after IRE has been performed, a contrast-enhanced CT will be made to assess adequate ablation. It is expected that patients will be discharged 24 to 36 hours after the IRE procedure. Before patient’s discharge, quality of life and postprocedural pain will be assessed through SF-36 questionnaire and VAS score respectively. At 1 week after the procedure, VAS score and SF-36 questionnaire will be obtained and cross-sectional imaging by CEUS and MRI will be performed.

**Figure 2 figure2:**
[figure not shown]
A. The NanoKnife IRE console. B. The console operates with 19G monopolar needle electrodes, which are bundled together using the external spacers.

#### Computed Tomography Imaging (Standard)

As provided per ablation protocol, CT imaging will take place during the diagnostic phase and during the procedure. According to our ablation surveillance protocol, follow-up CT imaging will be performed at 3 months, 6 months, 1 year, 1.5 year, 2 years, 2.5 years, and 3 years after IRE ablation. After this, patients will be followed up yearly up to 10 years. This is the standardized follow‐up after ablative therapy at our institution (see Figure 1). Patients with an eGFR below 60 mL/min/1.73 m^2^ will undergo pre- and posthydration in order to prevent contrast-induced nephropathy. Patients with an eGFR below 30 mL/min/1.73 m^2^ are excluded from CT imaging.

CT imaging will be performed in a supine position in a dual source CT system, SOMATOM Force (Siemens Medical Solutions), or in a Sensation 64-slice CT scanner (Siemens Medical Solutions). First, a survey scan from the upper border of the diaphragm to the ischium bone will be made. Next, noncontrast series in the same section will be performed. Subsequently, 120 mL of Ultravist-300 diluted with NaCl 0.9% will be administered intravenously with a speed of 4 mL/s. Following contrast injection, arterial, venous, and delayed series will be obtained after 45 seconds, 115 seconds, and 600 seconds, respectively. Source images will be recontructed in coronal and sagittal planes using multiplanar reconstruction in the venous and delayed series.

#### Contrast-Enhanced Ultrasound and Magnetic Resonance Imaging (Study Intervention)

Baseline CEUS will take place 1 day before IRE, and 1 week, 3 months, 6 months, and 12 months after IRE. MRI imaging will take place 1 week, 3 months, 6 months, and 12 months post-IRE (see Figure 1). This frequency was established in order to assess lesion size and characteristics.

CEUS imaging encompasses microbubbles of 3 to 5 µm as a contrast agent to visualize blood flow. The phospholipid-coated microbubbles demonstrate regional tissue vascularization, including the tissue-specific microvasculature. This study uses a Philips iU22 (Phillips Healthcare) device united with a third-generation intravenous ultrasound contrast agent (SonoVue) for optimal imaging. Sonovue contrast agent is characterized by a distribution half-life of 1 minute and an elimination half-life of 6 minutes when intravenously administired [29].

MRI will be performed with the patient in the supine position using a 1.5 Tesla AVANTO MRI scanner (Siemens Healthcare) with a 16-channel body matrix array coil. According to our kidney tumor protocol, a minimum of 9 sequences will be performed: T2-trufi with fat suppression, T1-fl2d contrast-enhanced in and out of phase, T2-haste, T1-vibe unenhanced, and dynamic series at 30 seconds, 60 seconds, and 15 minutes **.** Intravenous contrast agent Gadovist (Bayer Pharma) of 0.1 mmol per kg of body weight will be administered for enhancement.

### Sample Size

Our sample size was deliberated on the basis of previous similar study designs that used comparable sample sizes of 6 to 20 patients [20,23-25]. In this phase of research (phase 2B IDEAL Collaboration), a small cohort of N=20 was chosen to acquire first results in order to progress to a large trial. A sample size of 20 patients does not permit reliable comparative statistical analysis. In this study, IRE is intended as a curative therapy. Consequently, there will be no exploration in number of probes and configuration settings. Hence, analysis will be restricted to averages and standard deviations of assessed radiologic features.

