For the follow-up of renal masses, the most frequently used imaging modality is contrast-enhanced CT. Multiple studies have demonstrated that MRI and CEUS are adequate imaging techniques for follow-up after IRE [36-40]. However, the use of contrast-enhanced CT scan in the follow-up after kidney ablation might be precluded because of potential nephrotoxicity or ionizing radiation exposure in young patients. In the population of patients that receive ablation for their renal mass comorbidity, older age and decrease in renal function are common since their presence entails a clear indication for ablative therapy. Furthermore MRI, applicable to a broader range of the ablated population, may not be easy available and may increase costs. Hence, in this population it is vital to investigate whether other imaging modalities will detect recurrences and residual disease in renal masses with the same accuracy as CT and MRI.

Nononcological outcomes of IRE have been minimally investigated in renal tumors. A total of 2 small studies described serum creatinine levels and demonstrated no significant changes in renal function or transient increase of creatinine which resolved after 1 month [23,24]. Postprocedural pain and length of stay is described by Thomson et al in liver, kidney, and lung (N=36, kidney tumors n=4). While 4 patients were admitted longer than 24 hours, none of these patients had kidney tumors. Postprocedural pain was registered through analgesics use, demonstrating 2 patients who required intravenous or intramuscular analgesics. No patient required prolonged analgesic use after discharge. Quality of life has not been reported in current IRE literature. Insight in nononcological outcomes, including quality of life, is urgently required since treatment decision making is often influenced by this. Particularly in the ablation population, meaning elderly patients with multiple comorbidities, quality of life after an intervention is of great importance.

Categorized as a level 2b study according to the IDEAL classification, this study will provide prospective information on kidney IRE ablation with an extensive description on the radiological evolution of the ablated lesion along time as well as mid-term oncological outcomes. Lastly, we will provide prospective data on quality of life, kidney function, pain level, and duration of admittance after IRE.

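### The statement that 20 patients allow no reliable comparison is fair between groups but not within patients; the averages-and-SDs restriction leaves the promised change over time without a stated precision

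*Protocol article*

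**What the plan says.** The Sample Size section takes its number from precedent, citing "previous similar study designs that used comparable sample sizes of 6 to 20 patients", and says that "a small cohort of N=20 was chosen to acquire first results in order to progress to a large trial". It then states that "A sample size of 20 patients does not permit reliable comparative statistical analysis". Next it explains that IRE is given with curative intent and adds: "Consequently, there will be no exploration in number of probes and configuration settings". From this it concludes that "analysis will be restricted to averages and standard deviations of assessed radiologic features".

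The imaging schedule (Study Design and Study Procedures) follows the same patients over time. MRI is done at 1 week and at 3, 6 and 12 months. A contrast-enhanced CT is made directly after ablation, and CT is repeated at 3, 6 and 12 months. The Analysis section lists what the uroradiologist reads on each CT or MRI. Ablation-zone volume in cm³ is the one clearly continuous item, and no change from an earlier scan is listed. The closing part of the Discussion promises an "extensive description on the radiological evolution of the ablated lesion along time".

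**The concern.** The reason given just before the restriction is that probe numbers and settings will not be varied. That rules out comparing configurations. It says nothing about comparing a patient's 12-month scan with the same patient's 1-week scan, where the patient serves as his or her own control.

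Tumours of any size up to 4 cm are eligible and probe number is adapted to the tumour, so zone volumes will differ widely between patients. An SD at each visit mostly describes that spread. A reader of the later report who wants to know how far zones shrink, and how surely this is known, needs the SD of the change. That SD cannot be worked out from two visit SDs. The trial is meant to inform a larger one, for which the mean within-patient change and its SD would be useful outputs.

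**Working it through.** There is no power or precision figure in the article to reproduce, because N = 20 comes from precedent. The check is therefore what 20 patients can deliver for a change over time.

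**1. Precision of a paired change.** Half-width = t(0.975; 19) × SD of change / √20 = 2.093 / 4.472 = 0.468 SD of the change. If a test were wanted, 80% power is reached at 0.66 SD of the change.

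**2. Comparison with visit summaries.** Let both visits have the same SD and let ρ be the within-patient correlation, which the documents do not give. In units of the visit SD:
- visits read as independent means: t(0.975; 38) × √(2/20) = 2.024 × 0.316 = 0.64
- paired: 2.093 × √(2(1 − ρ)/20)

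| ρ | paired 95% half-width (visit-SD units) |
|---|---|
| 0 | 0.66 |
| 0.3 | 0.55 |
| 0.5 | 0.47 |
| 0.7 | 0.36 |
| 0.8 | 0.30 |
| 0.9 | 0.21 |

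Pairing gains nothing at ρ = 0. At 0.7 or more the gain is large.

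**3. Why visit SDs do not settle it: an illustration on assumed values.** Take spherical zones with diameters uniform from 1.5 to 4 cm and a mean shrinkage of 30% (patient SD 15 points). Simulation gives a mean volume of 13.1 cm³ (SD 9.1) at the first visit and 9.2 cm³ (SD 6.8) at the later one. The change is −0.30 × 13.1 = −3.9 cm³.
- Read as independent means: SE = √((9.1² + 6.8²)/20) = 2.54, half-width 2.024 × 2.54 = 5.1, 95% CI about −9.1 to +1.2.
- Paired: the simulated SD of change is 3.7, half-width 0.468 × 3.7 = 1.7, 95% CI about −5.7 to −2.2.
- From the two visit SDs alone, the SD of change could lie anywhere from 9.1 − 6.8 = 2.3 (ρ = 1) to √(9.1² + 6.8²) = 11.4 (ρ = 0).

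The mean change is the same in both readings. Only its precision differs.

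**4. Who is scanned.** The CT section excludes patients with eGFR below 30 from CT, and the section on benefits and risks says that only MRI and CEUS are done once eGFR falls below 30. The set of patients with CT can therefore change between visits. If m of 20 patients were scanned at random, the visit mean would move with a 95% range of about ±1.96 × CV × √((1/m)(1 − m/20)) although no zone had changed. Assumed tumour sizes give a volume CV of about 54% (zone 1 cm wider than a tumour of 1.5 to 4 cm) to 70% (the zones in step 3).
- m = 18: 1.96 × 0.0745 × CV = 8% to 10%
- m = 15: 1.96 × 0.129 × CV = 14% to 18%

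The documents give no expected number of missing scans, so these values of m are illustrations only. Change within patients who have both scans is free of this shift in patient mix.

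**The case against.** Four points on the other side carry weight.

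- **The wording leaves room.** The restriction names averages and SDs of the features; it does not say per visit and does not exclude change scores. The mean and SD of each patient's change are also an average and an SD, and with n they give the paired interval. This stands, and it makes the addition compatible with the plan. But the Analysis section lists features per scan only, and the blanket sentence on comparison steers away from within-patient change.
- **The context concerns configurations.** Read with its neighbouring sentences, the remark on comparison may have been meant only for groups or probe settings. If so, the rewording is a clarification.
- **Nothing is lost with complete data.** A reader might infer that visit averages hide the lesion's evolution altogether. They do not: with every scan present, the difference of visit means equals the mean within-patient change.
- **The first objective is untouched.** Recurrence and residual disease are judged by enhancement, most of the listed reader features are qualitative, and no decision rule depends on zone volume.

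A reader might also go further and say that the plan would miss real shrinkage in a given share of trials. The documents do not support this. No unpaired test is planned, and the answer follows the assumed tumour sizes: for the same 30% shrinkage, treating visits as independent detects it in about half of simulated trials under the wider-zone assumption and in about 10% under the one in step 3. Nor does the earlier retrospective series, with 15 and then 6 of 20 patients imaged, show that this prospective trial with scheduled imaging will lose as many.

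**Conclusion.** The point holds in a limited form. The unqualified statement is fair for comparisons between groups, devices or settings and too broad for change within patients. Averages and SDs, if reported as visit summaries, would give the promised evolution a mean but neither a precision nor individual courses, and would be exposed to changes in who is scanned.

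The one firm figure is the paired half-width of 0.47 SD of the change at n = 20. How much better this is than visit summaries depends on a correlation that the documents do not give. A high value is plausible for zone volume because tumour sizes vary, but that is a judgement. The volumes, shrinkage and missing-scan figures above are illustrations on stated assumptions. The point does not call for a larger sample or for hypothesis tests; the study can remain descriptive.

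**What to change.** In the Sample Size section, limit the sentence on comparative analysis to comparisons between groups, devices or settings. Then add, in substance:

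- Ablation-zone volume will also be summarised as each patient's change from a stated reference scan on the same modality. For MRI this is the 1-week scan. For CT it is either the scan made immediately after ablation or the 3-month scan, with the choice named in advance.
- At each later visit, the mean change, its SD and 95% CI will be given for patients with both scans, with their number, and individual courses will be shown.
- A log ratio will be used only if all volumes are above zero; otherwise the absolute or percent change.

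Averages and SDs of the features can stay as background description. Creatinine, eGFR and VAS are not radiologic features, so the restriction does not reach them. If they too are summarised as paired change from the pre-IRE value, VAS should use plain differences, since a pain score can be zero.

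The cost is some wording and a few lines of analysis. No new data, visits or patients are needed.

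### The rule limiting analysis to means and SDs of radiologic features contradicts the article's own objectives, and gives the recurrence and residual disease rate no measure of precision

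*Protocol article*

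**What the plan says.** Study Objectives lists four aims and ranks none of them as primary. The first is clinical efficacy, "assessed by the recurrence and residual disease rate" on follow-up imaging. The second is the use of CT, MRI and CEUS to show the ablation zone. The third covers perioperative outcomes: "renal function, measured by creatinine levels and estimated glomerular filtration rate (eGFR"), length of stay, quality of life, and pain by VAS and analgesic use. The fourth is safety and feasibility, through CTCAE adverse events.

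Sample Size explains that "a small cohort of N=20 was chosen to acquire first results in order to progress to a large trial", then states "A sample size of 20 patients does not permit reliable comparative statistical analysis". It adds that probe numbers and settings will not be explored, and concludes: "Hence, analysis will be restricted to averages and standard deviations of assessed radiologic features".

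The Analysis section lists imaging characteristics only. Results, however, announces early findings on residual disease, quality of life, safety and feasibility. The Conclusions part of the Discussion says "we will provide prospective data on quality of life, kidney function, pain level, and duration of admittance after IRE".

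**The concern.** The rule in Sample Size is narrower than the objectives, and it is worded as a limit, not as an example. A statistician who kept to it would not tabulate adverse events or summarise eGFR, SF-36, VAS or length of stay. One who reported those outcomes would depart from the published plan.

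For the recurrence and residual disease rate the problem is milder. An average of yes/no results is the rate, but the SD beside it does not tell the reader how far the rate can be trusted. The Discussion (Principal Findings) presents the study as groundwork for a large randomized trial. A bare 0 or 1 failure in 20 would therefore be passed on without its uncertainty.

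**Working it through.** **1. Scope: objectives set against the rule**

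| Outcome in Study Objectives | Radiologic feature? | Allowed by the rule, read literally? |
|---|---|---|
| Recurrence and residual disease | Yes; both are on the imaging list in Analysis | Yes, but only as mean and SD |
| Ablation zone on CT, MRI, CEUS | Yes | Yes |
| Creatinine, eGFR | No | No |
| Length of stay | No | No |
| Quality of life (SF-36) | No | No |
| Pain (VAS, analgesic use) | No | No |
| CTCAE adverse events | No | No |

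No other section widens the rule.

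**2. Does the stated reason lead to the rule?** The two premises are that comparative analysis is unreliable at 20 patients and that device settings will not be varied. A proportion in one arm, a table of adverse events or a change in creatinine compares no groups. The premises support leaving out comparative tests. They do not support leaving out these summaries.

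**3. What an SD adds to a yes/no outcome.** With x events in 20, the mean is p = x/20 and the sample SD is √[p(1−p)·20/19].

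- 1/20: p = 0.05, SD = √(0.0475·20/19) = 0.224
- 2/20: p = 0.10, SD = √(0.09·20/19) = 0.308
- 4/20: p = 0.20, SD = √(0.16·20/19) = 0.410

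The SD is a function of p alone for given N, so it carries no further information. Several other items on the Analysis list are also categorical (shape of the zone, damage to nearby structures) and are no better served.

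**4. What an exact interval shows.** The article gives no expected rate and no confidence level, so the event counts and the 95% level are assumptions. The Clopper-Pearson limits are the 0.025 quantile of Beta(x, n−x+1) and the 0.975 quantile of Beta(x+1, n−x). For x = 0 the lower limit is 0 and the upper limit is 1 − 0.025^(1/n).

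| Events / evaluable | Rate | Exact 95% CI |
|---|---|---|
| 0/20 | 0% | 0 to 16.8% |
| 1/20 | 5% | 0.1 to 24.9% |
| 2/20 | 10% | 1.2 to 31.7% |
| 3/20 | 15% | 3.2 to 37.9% |
| 4/20 | 20% | 5.7 to 43.7% |
| 0/18 | 0% | 0 to 18.5% |
| 0/15 | 0% | 0 to 21.8% |

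The last two rows show that the 16.8% limit holds only if all 20 patients are evaluable. This matters here because the Introduction criticises an earlier retrospective series for having 1-year imaging in only 6 of its 20 patients.

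**5. The sample size itself.** There is no figure to reproduce: "Our sample size was deliberated on the basis of previous similar study designs that used comparable sample sizes of 6 to 20 patients". No alpha, power, effect size or precision target is claimed.

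**The case against.** The strongest reply is that the sentence means only that the analysis is descriptive. It follows directly on the remark about comparative analysis, the study schedule collects creatinine, VAS, SF-36 and CTCAE data, and the article commits itself elsewhere to reporting them. This is a fair account of the likely intent. A reader might infer that the sponsor plans to discard safety and quality of life, and the documents do not support that. But the sentence says something narrower than the intent, and nothing in the article corrects it.

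A reader might also infer that the trial's primary objective has no valid analysis. That goes too far on two counts. The article labels no objective primary. And residual tumor and recurrence are on the imaging list in Analysis, while the Limitations section rests success on imaging alone, so the rate lies inside the rule and its average is the right point estimate. What is wrong for this objective is the unsuitable SD and the lack of any measure of precision.

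Nor is N=20 an error. It is openly based on precedent in an exploratory phase and claims no precision that could be wrong.

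Finally, tabulation and interval methods commonly sit in a full protocol or SAP, neither of which is shown. That would answer a complaint about silence. It does not answer an explicit restriction that conflicts with the article's own objectives.

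**Conclusion.** The point holds as a contradiction within the article. Read literally, the Sample Size sentence excludes adverse events, renal function, quality of life, pain and length of stay, all of which Study Objectives sets out to evaluate. For those outcomes the conflict is complete. For the recurrence and residual disease rate the defect is smaller: mean and SD is a poor summary that hides an interval reaching 16.8% after 0/20 and 24.9% after 1/20, or 21.8% after 0/15. These figures assume an exact two-sided 95% interval, one yes/no result per patient, and illustrative event counts.

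This is one badly scoped sentence that should be corrected. It is not a fault in the design, the sample size or the data collection.

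**What to change.** Replace the last sentence of Sample Size with wording such as:

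> Analysis is descriptive, with no comparative testing, and covers all objectives. Residual or recurrent disease by 12 months is reported as n/N with an exact two-sided 95% CI. The number of patients with 12-month imaging is stated; those without it are shown separately and not counted as disease-free. Adverse events are reported as n/N by CTCAE grade. Creatinine, eGFR and VAS are summarised by visit and as change from the preoperative value, analgesic use as n/N, and SF-36 by visit. Length of stay and ablation volume are given as mean (SD) or median (IQR).

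Three notes go with it.

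- **SF-36:** change from baseline should be promised only if a questionnaire is collected before IRE. Study Design names imaging, creatinine and VAS as preoperative measures, and the procedure section first mentions SF-36 before discharge, after treatment.
- **Precision:** if the article states what N=20 delivers, it should say that 0/20 gives an upper limit of 16.8% only with all 20 evaluable, and about 21.8% for 0/15.
- **Event definition:** Study Design calls for a biopsy when imaging is suspicious, while Limitations bases success on imaging alone. The two should be reconciled so that the numerator is unambiguous.

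The cost is one paragraph and a little more analysis work. The drawback is that the reported evidence will look less firm, because the wide interval becomes visible.
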